#### **Data Safety and Monitoring Board (DSMB)**

The DSMB will monitor data collection and will be composed of a chair ([name]) and four other members. DSMB members and their backgrounds are presented in the table below.

| Name               | Position Title and Primary Affiliation                                                                              | Background and Expertise                                                                                        |
|---------------------------|----------------------------------------------------------------------------------------------------------------------------|------------------------------------------------------------------------------------------------------------------------|
| [name]            | Director of the Center for Mobility and Rehabilitation Engineering Research (CMRER) at the Kessler Foundation              | Clinical trial operation and data management, motor control, biomechanics and neuroimaging in health and disease.      |
| [name] | Assistant Director for Neuroscience Research, Center for Traumatic Brain Injury, Kessler Foundation                        | MRI study design, MRI data preprocessing and analysis, clinical trials, patient populations                            |
| [name], D. Phil   | Director of the Rocco Ortenzio Neuroimaging Center, Kessler Foundation                                                     | MRI safety, neuroimaging acquisition, sequence design, and MRI data preprocessing and analysis                         |
| [name]           | Associate Research Scientist, Department of Biomedical Imaging, Yale School of Medicine                                    | MRI safety, neuroimaging acquisition, sequence design, MRI data preprocessing and analysis, and data quality assurance |
| [name], OTR/L PhD | Professor, Director of Post-Professional Programs, Department of Occupational Therapy, NYU Steinhardt, New York University | Clinical trials, rehabilitation, occupational therapy                                                                  |

Once data collection begins, the PI will complete five forms quarterly (see below) detailing participant accrual and any adverse events and submit these forms to the DSMB for review. The PI will relay information from the DSMB to the IRB as a memo during the annual review.

### 1. Enrollment Monitoring Form

| Month | Number targeted | Number screened | Number enrolled | Number withdrawn or lost to follow-up | Number completing the study | Average age and SD of screened out participants | Number of women in screened out sample | Number of men in screened out sample |
|-------|-----------------|-----------------|-----------------|---------------------------------------|-----------------------------|-------------------------------------------------|----------------------------------------|--------------------------------------|
|       |                 |                 |                 |                                       |                             |                                                 |                                        |                                      |
|       |                 |                 |                 |                                       |                             |                                                 |                                        |                                      |
|       |                 |                 |                 |                                       |                             |                                                 |                                        |                                      |
|       |                 |                 |                 |                                       |                             |                                                 |                                        |                                      |

### 2. Participant Status Form

| Patient ID | Consent Date | Baseline Assessment (T0) Date | Treatment Completion Date | Immediate Follow-Up (T1) Date | One-month Follow-Up (T2) Date | Three-month Follow-Up (T3) Date | Reason for not completing the study |
|------------|--------------|-------------------------------|---------------------------|-------------------------------|-------------------------------|---------------------------------|-------------------------------------|
|            |              |                               |                           |                               |                               |                                 |                                     |
|            |              |                               |                           |                               |                               |                                 |                                     |
|            |              |                               |                           |                               |                               |                                 |                                     |
|            |              |                               |                           |                               |                               |                                 |                                     |

### 3. Total Enrollment Report Form

|                    | Female | Male | Total |
|--------------------|--------|------|-------|
| Ethnicity          |        |      |       |
| Hispanic or Latino |        |      |       |

|                                 |  |  |  |
|---------------------------------|--|--|--|
| Not Hispanic or Latino          |  |  |  |
| Unknown                         |  |  |  |
| Total                           |  |  |  |
|                                 |  |  |  |
| Racial Category                 |  |  |  |
| American Indian / Alaska Native |  |  |  |
| Asian                           |  |  |  |
| Native Hawaiian / Other         |  |  |  |
| Pacific Islander                |  |  |  |
| African American                |  |  |  |
| White                           |  |  |  |
| More than one race              |  |  |  |
| Unknown                         |  |  |  |
| Total                           |  |  |  |

#### 4. Demographic Characteristic by Group

|                                 | Treatment Group | Control Group |
|---------------------------------|-----------------|---------------|
| Sex                             |                 |               |
| Male                            |                 |               |
| Female                          |                 |               |
| Ethnicity                       |                 |               |
| Hispanic or Latino              |                 |               |
| Not Hispanic or Latino          |                 |               |
| Unknown                         |                 |               |
|                                 |                 |               |
| Racial Category                 |                 |               |
| American Indian / Alaska Native |                 |               |

|                                 |  |  |
|---------------------------------|--|--|
| Asian                           |  |  |
| Native Hawaiian / Other         |  |  |
| Pacific Islander                |  |  |
| African American                |  |  |
| White                           |  |  |
| More than one race              |  |  |
| Unknown                         |  |  |
|                                 |  |  |
| Age (in years): mean (SD)       |  |  |
| Education (in years): mean (SD) |  |  |

## 5. Adverse Events Form

| Participant ID | Adverse Event | Onset Date | Ending Date | Severity | Relation to study | Action | Outcome | Comments |
|----------------|---------------|------------|-------------|----------|-------------------|--------|---------|----------|
|                |               |            |             |          |                   |        |         |          |
|                |               |            |             |          |                   |        |         |          |
|                |               |            |             |          |                   |        |         |          |
|                |               |            |             |          |                   |        |         |          |

Codes:

Severity:

1=Mild

2=Moderate

3=Severe

4=Life threatening

Relation to study:

0=Definitely unrelated

1=Unlikely to be related

2=Possibly related

3=Probably related

4=Definitely related

## C. Analysis

All variables will be examined for outliers and appropriate strategies will be instituted if problems are identified. AET+PMT and Stretching+PMT will be compared on demographic and baseline variables (including baseline hypoperfusion) using two-sample t tests, Chi-square, or

equivalent non-parametric tests, as appropriate. Effect sizes (ES) will be calculated for all primary and secondary analyses. As recommended by Hahn (Hahn, 2012) for active control trials, we will conduct both intent-to-treat and per-protocol analyses and conclude AET+PMT superiority on the primary outcomes if both analyses support it. Per-protocol analyses will be conducted in those completing follow-up testing and in those who demonstrated good adherence and compliance. We will define adherence/compliance as completing at least 34 of the 40 possible treatment sessions as prescribed. This approximates the 85% adherence guideline for internal validity for RCTs based on the Physiotherapy Evidence Database (PEDro) scale. (Sherrington et al., 2000) Should attrition exceed expectations, we will use two-sample t-tests, Chi-square tests, or non-parametric equivalents to compare all baseline variables between subjects who remain in the study and those who drop out. Further specific analyses are described below.

#### Univariate analyses:

*Behavioral data:* To measure the impact of treatment we will use a 2x2 repeated measures design assessing whether participants in the AET+PMT condition improve more from baseline to outcome than those in the Stretching+PMT condition. The reading tests (RCBA, reading aloud, touchscreen tests) will serve as primary outcomes and other language tests (WAB-R, PNT, CAT-DQ) as secondary outcomes. Improvement would be indicated by a significant condition by session interaction. We will also evaluate the within-subjects effect of PMT on reading improvement (post-treatment > baseline).

*Cerebral Blood Flow (CBF) data:* To examine the immediate effect of aerobic exercise on cerebral hemodynamics we will compare CBF measured with Arterial Spin Labeling (ASL) scans (used to measure cerebral circulation) at baseline (T1) with CBF measured after 20 min of moderate to vigorous intensity aerobic exercise (or 20 min of light stretching, T2).

ASL provides a non-invasive absolute (mL (blood volume)/100g (tissue volume)/min (time)) measure of CBF, that is suitable even for patients who may have impaired kidney function and cannot undergo contrast-based perfusion MRI (Zaharchuk, 2014). In ASL, water molecules are labeled with a magnetic pulse before they enter the brain through the arterial blood supply. The effect of labeling can be quantified by characterizing the interaction of blood flow and label decay. (Detre et al., 1998, 2012) Thus, ASL will be used to provide a measure of CBF changes as a function of AET. It is well known that stroke and cardiovascular disease can cause deficits in temporal dynamics of blood flow (Roc et al., 2006; Treger et al., 2007). Furthermore, Altamura et al. (Altamura et al., 2009) reported that delays in the hemodynamic signal are associated with worsened cerebral autoregulation (maintenance of constant blood flow despite changes in arterial blood pressure). For this reason, in addition to changes to regional and global CBF, we will evaluate the spatial coefficient of variation (sCoV) in the ASL signal as an indirect measure of arterial transit time, as proposed in Mutsaerts et al. (Mutsaerts et al., 2017), because prolonged transit times lead to proportion of the ASL signal remaining in conduit arteries at the time of

imaging and result in spatially varying CBF image intensity. Importantly, to account for longer transit times, we will use longer inversion time (TI=2000ms), recommended for stroke imaging. Additionally, calculating sCoV will allow us to account for different transit times when estimating CBF. Detailed medication history along with respiration and heart rate data will also be collected to serve as regressors.

ASL data will be processed using the Oxford FMRIB Software Library (FSL). Brain extraction will be performed using BET, and ASL data will be registered to the structural image using FLIRT with 6 degrees of freedom, normalized mutual information cost function, and sinc interpolation.(Jenkinson et al., 2002) Tag-control ASL images will be motion corrected using MCFLIRT.(Jenkinson et al., 2002) To quantify perfusion in absolute units (ml/100 g/min), we will apply kinetic model inversion within the oxford\_asl software.(Chappell et al., 2009) A single delay pASL model will be used for analysis. Calibration will be performed using a single M0 pretag image value with CSF reference. We will apply spatial smoothing to improve ASL signal and partial volume correction to account for perfusion in voxels partly occupied by both white and gray matter.(Chappell et al., 2011) Partial volume estimates will be created using white and grey matter masks derived from each patient's segmented structural brain image. Lesion CBF will be excluded. The resulting ASL images will be normalized to individual mean white matter perfusion. For group analyses, transformation matrices for each patient's structural brain to the MNI152\_1mm template will be applied to the normalized ASL images to bring them into a common atlas space. Binarized masks from the Gordon atlas of 333 functionally-defined gray matter regions of interest (ROI)(Gordon et al., 2016) will be applied to the data for the analysis of regional CBF changes using repeated measures ANOVA. Whole-brain CBF changes will also be examined using FSL package for permutation testing (RANDOMISE).(Winkler et al., 2014)

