## **2. OBJECTIVES OF THE STUDY**

This study has 3 objectives:

1. To determine if the proposed intervention will improve language outcomes.
2. To examine the immediate impact of aerobic exercise on cerebral circulation
3. To examine the neural mechanisms of sustained change in reading outcomes following the proposed intervention.

To address Objective 1, we will randomize 100 chronic (>3 months post-stroke) left hemisphere stroke participants to either the aerobic exercise (AET) or the stretching condition. The AET condition will complete 20 minutes of moderate intensity aerobic exercise in the form of stationary bike cycling prior to a 1.5-hour targeted reading treatment session using phono-motor therapy (PMT) (Kendall et al., 2019). The control condition will complete 20 minutes of light

stretching before each PMT session. Both conditions will also have a 5-min warm up and cold down. All participants will complete 40, 2-hour intervention sessions administered 3-5 times per week for 8-10 weeks. We will measure reading competence as the primary outcome, and naming, auditory comprehension, and spontaneous speech as secondary language outcomes using standardized and experimental tasks administered before and after the full course of treatment. We expect a condition by time interaction, such that the AET condition will improve more than the stretching condition from baseline to end of treatment.

To address Objective 2, we will ask participants to undergo 2 MRI scans, one at baseline and one following the first AET or stretching session. The scans will assess regional and whole brain cerebral blood flow and functional connectivity to determine the immediate impact of aerobic exercise vs. stretching on neural and vascular processes. A greater increase in cerebral blood flow is expected after aerobic exercise than stretching.

To address Objective 3, we will ask participants to complete language testing and a 3rd MRI scan after completing the intervention. We expect greater increases in cerebral blood flow, brain connectivity, and task-related activation in the AET condition compared to the stretching condition. These increases are expected to be most evident in areas supporting phonology and orthography-to-phonology mapping. The increased cerebral circulation and brain activity are expected to predict reading and other language outcome gains.

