## B. Research Procedures

- Following screening, participants will be randomly assigned to one of 2 exercise conditions: aerobic exercise (cycling) or control (light stretching).

Participants will then undergo baseline assessments, treatment, and outcome assessment. They will also complete 3 MRI scans as detailed below.

- Patients will be tested for phonological, orthographic, and semantic impairments using a two-alternative forced choice touch-screen paradigm (Boukrina et al., 2020). On semantic trials, the target is a concrete noun presented at the top of the screen. The two choices on the bottom include a close semantic neighbor that has high feature similarity to the target and a more distant semantic neighbor. Patients are instructed to select the word that is most similar in meaning to target (Fig.1). On phonological tasks, all letter strings are pseudowords and the task is to select the string that rhymes with the target at the top. The choices include a close rhyme of the target with non-matching orthography and a close, but implausible rhyme. There are both a word and a picture version of these tasks. In the orthographic task, all letter strings contain consonant doublets that are part of a trigram with high or low (position-constrained) frequency. Participants are asked to identify which string looks more like it could be a word (task and stimuli adapted from Cassar &

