### Semantic      Phonological      Orthographic

|                |                |                |
|----------------|----------------|----------------|
| goose          | gake           | beff      ffeb |
| lamb      swan | daik      jeak |                |

Figure 1. Example trials in the behavioral task administered to patients.

Treiman 1997). Patients will also complete a reading aloud task, in which they will be asked to read single words, with varying lexical characteristics, as well as pseudowords.

- Patient demographics will be collected using a self-report questionnaire. The PI will assist patients in completing the questionnaire and where necessary will contact family members for additional information.
- Participants will complete the Reading Comprehension Battery for Aphasia (RCBA-2nd edition), and, additionally, will complete will include the Western Aphasia Battery, Revised (WAB-R) (Kertesz, 2007), the Philadelphia Naming Test (PNT) (Walkera and Schwartz, 2012), and self-reported ratings of language disability from the Comprehensive Aphasia Test Disability Questionnaire (CAT-DQ) (Swinburn et al., 2004) .
- We will also assess depression via the Geriatric Depression Scale (Yesavage et al., 1982) (5 min), spatial neglect via the Behavioral Inattention Test-conventional(Halligan et al., 1990) (15 min), and screen for other cognitive deficits using the Oxford Cognitive Screen (OCS) (Demeyere et al., 2015) (1 hour). If found different between conditions, these tests will be used as covariates when examining the effects of intervention on behavioral and neural outcomes. A 10-meter walk test (Moore et al., 2018) and a 6-min walk test (Kosak and Smith, 2005) will be administered to measure the impact of the AET and stretching interventions on mobility (gait speed and walking distance).

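### The protocol names one primary outcome in section 2 and several in section 5C, and its superiority rule does not say how many of them must succeed

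*Protocol*

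**What the plan says.** Section 2 (Objectives) uses the singular: "We will measure reading competence as the primary outcome". It does not say which test or score stands for that construct.

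Section 5C (Univariate analyses, behavioral data) uses the plural: "The reading tests (RCBA, reading aloud, touchscreen tests) will serve as primary outcomes". The criterion follows: "Improvement would be indicated by a significant condition by session interaction".

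Section 5B (Research Procedures) shows what these tests contain:

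- Touchscreen: "Patients will be tested for phonological, orthographic, and semantic impairments using a two-alternative forced choice touch-screen paradigm". After the semantic and phonological tasks it adds: "There are both a word and a picture version of these tasks".
- Reading aloud: "they will be asked to read single words, with varying lexical characteristics, as well as pseudowords".
- RCBA: "Participants will complete the Reading Comprehension Battery for Aphasia".

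The only decision rule is in the opening paragraph of section 5C. After requiring both intent-to-treat and per-protocol analyses, it says the trial will "conclude AET+PMT superiority on the primary outcomes if both analyses support it".

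**The concern.** A superiority trial needs a reader to be able to tell, before the data exist, which result would count as success. Here two things are unsettled. The primary outcome is one construct in section 2 and a set of tests in section 5C, with no composite linking them. The superiority rule joins two analysis sets but does not join the outcomes.

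Suppose one reading score separates the arms and the others do not. On the protocol text, one author could report superiority and another could report failure, and both could cite section 5C. An any-one reading raises the false-positive rate of the headline claim. An all-must-succeed reading protects it but makes the trial much harder to win. These are very different trials, and the protocol does not choose between them.

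**Working it through.** **No figure to reproduce.** The protocol gives no alpha, sidedness, power, effect size or SD for this comparison. Every size below therefore rests on labelled assumptions.

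**Step 1: count the scores (sections 5B and 5C).**
- Families named: RCBA, reading aloud, touchscreen = 3.
- With the three touchscreen tasks scored separately: 1 + 1 + 3 = 5.
- If words and pseudowords are also scored separately, and the semantic and phonological tasks each give a word and a picture score: 1 + 2 + (2 + 2 + 1) = 8.

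The protocol does not state the scoring. Three is the least that section 5C lists, five is the natural count from the task descriptions, and eight is a possibility.

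**Step 2: error if any one success is enough.**

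Assumptions:
- two-sided 0.05 per score
- 100 participants (section 5A) split 50 per arm
- pairwise correlation 0.5 between change scores
- per-protocol set a random 85% or 70% of each arm
- no true effect

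A t-test on change scores is equivalent to the 2×2 condition-by-session interaction. A false claim is counted only if the same score favours aerobic exercise significantly in both analysis sets. Simulation gives:

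| Scores | Per-protocol 85% | Per-protocol 70% |
|---|---|---|
| 1 | 1.6% | 1.2% |
| 3 | 4.2% | 3.2% |
| 5 | 5.7–6.2% | 4.6–4.7% |
| 8 | 8.4% | 6.9% |

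The ranges for five scores come from separate runs, which differ by a few tenths of a point. In round terms: 3–4% for three, 5–6% for five and 7–8% for eight, against about 1.5% for one.

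**Step 3: sensitivity to correlation (five scores, same counting).**

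| Correlation | Per-protocol 85% | Per-protocol 70% |
|---|---|---|
| 0 | 7.9% | 6.1% |
| 0.3 | 6.8% | 5.2% |
| 0.5 | 6.2% | 4.7% |
| 0.7 | 5.0% | 4.1% |
| 0.9 | 3.4% | 2.9% |

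**Step 4: the other reading, all must succeed.** Error cannot exceed that of a single score. Power falls instead. If each score had 80% power and the scores were independent, all would succeed with probability 0.8³ = 0.51 for three and 0.8⁵ = 0.33 for five. Positive correlation softens this loss but does not remove it.

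**Step 5: cost of an adjustment.** The standardised difference detectable at 80% power with 50 per arm is (z for alpha + 0.842) × √(2/50), where √(2/50) = 0.2.
- Alpha 0.05: (1.960 + 0.842) × 0.2 = 0.56.
- Alpha 0.05/5 = 0.01, the first Holm step for five scores: (2.576 + 0.842) × 0.2 = 0.68.

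**The case against.** **The protocol does not say that one success is enough.** This is correct. The rule speaks of the primary outcomes in the plural, with no word meaning any of them, and can be read as requiring all. A reader might infer that the protocol licenses a claim on the best of several scores. The text does not support that inference. It supports only that the rule is open.

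**Larger error rates do not apply.** A reader might compute 1 − 0.95³ = 14%, 1 − 0.95⁵ = 23% and 1 − 0.95⁸ = 34%. Those figures assume independent scores and count results favouring stretching, which cannot support superiority of aerobic exercise. They also leave out the requirement that both analysis sets agree. The figures in the working avoid all three problems and are much lower.

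**The criterion might seem to have no direction.** The interaction sentence alone states none. But section 2 expects the aerobic arm to improve more, the sentence that opens the behavioral analysis asks the same question, and the conclusion in section 5C is superiority of that arm. Direction is settled.

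**The detail may sit in a statistical analysis plan.** Scoring and multiplicity adjustment are often placed there, and none is shown, so it cannot be said that the trial lacks error control. What stands is narrower. This protocol itself undertakes to name the primary outcome and to state when superiority is concluded. It names the outcome differently in two places and states a rule that cannot be applied without a further choice.

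**Reading competence may be a construct measured by several tests.** That is a fair reading of section 2, and it reduces the conflict in wording. It still leaves the protocol without a rule that turns several results into one conclusion.

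**Conclusion.** The point holds as a defect in how the protocol fixes its primary outcome and success condition. Sections 2 and 5C do not agree on the number of primary outcomes, and the superiority rule in section 5C does not say whether one, some or all must succeed. Confidence in this is high, because it rests on the text alone.

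Confidence in the size is lower. Under an any-one reading and the assumptions in the working, a false claim for aerobic exercise is roughly two to three times as likely with three scores as with one under the same rule, about four times with five, and five to six times with eight. Measured against the usual 2.5% in one direction, the excess is small for three scores and about twofold for five. At correlation near 0.9 it is slight. The tasks are described as probing distinct impairments, so a correlation that high should not be presumed. The per-protocol set was treated as a random subset, which real adherence need not be.

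**What to change.** Use the same wording in section 2 and in both parts of section 5C (the superiority rule and the behavioral analysis).

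- **Preferred:** name one reading score, or one pre-defined composite such as the mean of baseline-standardised scores, as the single primary outcome. Make the other reading scores secondary. State the alpha.
- **If several must stay primary:** list the exact scores, including how touchscreen versions and words versus pseudowords are scored. State the alpha and the combination rule, either Holm across the list or a requirement that all succeed.

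A single score or composite costs only wording, if settled before outcome data are seen. Holm over five scores is not free: its first step is 0.01, which raises the detectable standardised difference from about 0.56 to 0.68 with 50 per arm. Requiring all to succeed needs no adjustment but lowers the chance of a positive trial, so power should be checked before choosing it.

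### The pre-post change in reading cannot be called an effect of PMT when every participant receives PMT, and the follow-up visits and T1/T2/T3 labels need reconciling

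*Protocol*

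**What the plan says.** **Treatment and randomisation.** Section 5.B of the Protocol says that "participants will be randomly assigned to one of 2 exercise conditions: aerobic exercise (cycling) or control (light stretching". Section 2 has the control arm doing "stretching before each PMT session", and adds: "All participants will complete 40, 2-hour intervention sessions administered 3-5 times per week for 8-10 weeks". PMT is thus common to both arms.

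**Behavioural analysis.** Section 5.C, Univariate analyses, sets up a 2x2 repeated measures design to assess "whether participants in the AET+PMT condition improve more from baseline to outcome than those in the Stretching+PMT condition", judged by the condition by session interaction. It then adds a second analysis: "We will also evaluate the within-subjects effect of PMT on reading improvement (post-treatment > baseline".

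**Timing.** Objective 3 in section 2 is "To examine the neural mechanisms of sustained change in reading outcomes following the proposed intervention". The same section places language testing before and after the course of treatment, with a third MRI after it. Section 5.A gives three scans: before treatment, after one session, and after treatment. The Participant Status Form in section 5.B nevertheless has a column headed "One-month Follow-Up (T2) Date" and another for a three-month follow-up, labelled T3. In section 5.C, T2 is a different occasion: the scan after the first 20 minutes of exercise ("or 20 min of light stretching, T2").

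**The concern.** A randomised comparison can isolate only what differs between the arms, and here that is the exercise condition. The added pre-post analysis names PMT as the cause of a change that has no comparator. Other explanations come from the design itself: the same tests are given before and after; entry is allowed from 3 months after stroke, with no upper limit and no stable-baseline requirement; participants are chosen for having a reading deficit; and half do cycling and half stretching alongside PMT. A significant result could then be reported as evidence that PMT works. No model choice in a statistical analysis plan can recover a PMT effect from these data.

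The visit schedule is a separate and smaller matter. The monitoring form implies data at one and three months that no procedure collects and no analysis uses. Section 5.C also defines the per-protocol set partly by completion of follow-up testing without saying which follow-up, and the superiority rule needs that analysis to agree with intent-to-treat. If the same label denotes different occasions in different places, the set and the contrasts can be read in more than one way.

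**Working it through.** The Protocol states no effect size, standard deviation, alpha or power for the pre-post analysis, so there is no figure of its own to reproduce.

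**1. What the two contrasts estimate.** Let D be the change common to both arms from practice, recovery and similar sources, P the effect of PMT, A the effect of cycling and S the effect of stretching.

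- Expected change, AET+PMT: D + P + A
- Expected change, Stretching+PMT: D + P + S
- Interaction (difference in change): A − S. D and P cancel.
- Pre-post change averaged over equal arms: D + P + (A + S)/2. P cannot be separated from D, A and S.

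**2. Illustration of the pre-post test with P = 0.** The sample size of 100 is from section 5.A. Assumptions: all 100 are analysed, two-sided alpha 0.05, and a common drift dz expressed as mean change divided by the standard deviation of change. The probability of a significant gain is Φ(dz × √n − 1.96), with √100 = 10.

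- dz = 0.1: Φ(1 − 1.96) = Φ(−0.96) = 17%
- dz = 0.2: Φ(2 − 1.96) = Φ(0.04) = 52%
- dz = 0.3: Φ(3 − 1.96) = Φ(1.04) = 85%

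With 85 analysed instead (an assumed figure), the results are 15%, 45% and 79%. The randomised interaction stays at 5% when the drift is the same in both arms and A = S.

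**3. Regression to the mean, as one component of D.** Suppose selection is on the observed baseline score below c standard deviations, with test reliability r (both assumed). Put λ = φ(c)/Φ(c). The expected gain is (1 − r)λ, and the standard deviation of change is √[(1 − r)²(1 − cλ − λ²) + 1 − r²].

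- r = 0.8, c = 0: λ = 0.798, gain 0.160, SD of change 0.612, dz = 0.26, significant gain in 74%
- r = 0.9, c = 0: gain 0.080, SD of change 0.440, dz = 0.18, 44%
- r = 0.8, c = −1: dz = 0.50, over 99%
- r = 0.8 or 0.9, c = +1: about 15% or 10%
- Selection on a separate screening measurement with independent errors: expected gain zero, and two-sided rejection about 5% at any r or c

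**4. Visit labels side by side.**

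| Label | Participant Status Form | Section 5.C |
|---|---|---|
| T0 | Baseline | not used |
| T1 | Immediate follow-up | Baseline scan |
| T2 | One-month follow-up | Scan after first exercise or stretching |
| T3 | Three-month follow-up | Scan compared with T1 for Aim 3; by Objective 3, after treatment |

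T1, T2 and T3 each mean something different in the two places.

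**The case against.** The strongest reply is that the pre-post analysis is only supplementary. The stated rule for superiority rests on the exercise comparison, and section 2 already expresses Objective 1 as a condition by time interaction, which common drift does not bias. All of this stands, and it limits the consequence. It does not make the label *effect of PMT* supportable.

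Two stronger readings may tempt a reader, and the documents do not support them.

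- *The pre-post test will probably be significant even if PMT does nothing.* The high regression-to-the-mean figures require selection on the baseline outcome score itself, with a cutoff at or below the mean of the candidates. Section 5.B puts screening before random assignment and baseline assessment after it. If screening is a separate measurement, this source may be negligible. The Protocol gives no cutoff or reliability and also uses self-report for entry. Practice and recovery remain, but their size is unknown.
- *Nothing is scheduled after treatment, so Objective 3 has no data.* The Participant Status Form does list later visits. Moreover, *sustained* may only contrast with the immediate effect in Objective 2, in which case the post-treatment tests and scan serve it. The abstract mentions retention, but as part of the rationale and not as a listed outcome. What stands is an unreconciled schedule and an undefined term.

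It is also fair to say that the form prints the visit name beside each label and that section 5.C defines T1 and T2 where it introduces them. Actual confusion of visits is a possibility, not a demonstrated error.

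**Conclusion.** The concern holds for the attribution. Since PMT is given to all participants and no comparison without it is described, pre-post change can be reported as change during the programme but not as an effect of PMT. This conclusion follows from the design and needs no numerical assumption. The numerical size cannot be established from the documents: the range of 17% to 85% depends wholly on an assumed drift of 0.1 to 0.3 standard deviations of change, 100 analysed participants and two-sided alpha 0.05. It should not be read as a forecast. The randomised test of aerobic exercise is sound on this point.

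On timing, the supportable conclusion is an internal inconsistency. The form's one- and three-month visits are absent from the objectives, procedures, MRI schedule and 2x2 analysis, and its T1, T2 and T3 conflict with those of section 5.C. As written, no described analysis addresses durability after the end of treatment.

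**What to change.** - In section 5.C, rename the pre-post analysis as descriptive change during the programme (PMT with cycling or stretching), reported with a confidence interval and without a claim that PMT is effective.
- State that the conclusion for Objective 1 is limited to the added effect of AET over stretching.
- Settle the later visits. If they are held, describe their tests in section 5.B and their analysis in section 5.C. If not, delete the two columns from the form and word Objective 3 as change at end of treatment.
- Say which assessment the per-protocol definition means by follow-up testing.
- Use one set of visit labels in the form and the analysis section.

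If the later visits are not held, these are changes of wording in the Protocol and one form, with no effect on recruitment, treatment or the primary comparison. If they are held, the added work is to write down their tests and analysis. The downside is that the trial claims slightly less.
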